## Abstract

**Background:**

Lower urinary tract symptoms related to benign prostatic obstruction (BPO) are frequent in men aged > 50 years. Based on the use of innovative medical devices, a number of transurethral ablative techniques have recently been developed for the surgical treatment of BPO. In recent years, GreenLight photoselective vaporization of the prostate (PVP) has been considered as a non-inferior alternative to transurethral resection of the prostate. The GreenLight PVP is usually considered as an interesting surgical option for patients treated via oral anticoagulants (OACs) with regard to its haemostatic properties. The aim of this study was to assess the impact of maintaining OAC treatment in patients undergoing PVP.

**Methods:**

This study is a multicentre, open-label, randomized controlled trial (RCT) designed to show the non-inferiority of PVP surgery in patients with BPO treated with OACs. This study is designed to enrol 386 OAC-treated patients (treated with vitamin K antagonists and direct oral anticoagulants) who are undergoing PVP for BPO. Patients will be randomized (1:1) to either maintain or stop OAC treatment during the perioperative course. The intervention group will maintain OAC treatment until the day before surgery and resume OAC treatment the day after surgery, whereas the control group will stop OAC treatment (with or without low-molecular-weight heparin bridging therapy) according to the anaesthesia guidelines. The primary outcome of interest to be assessed is the 30-day complications rate according to the Clavien-Dindo classification. The secondary endpoint will examine the 30-day rate of haemorrhagic and thrombotic events. This study will provide 80% power to show non-inferiority, defined as not worse than a 10% (non-inferiority margin) inferior change in the proportion of patients with good outcomes (Clavien-Dindo score < 2), using two-tailed 95% confidence intervals.

**Discussion:**

This first multicentre RCT in the field is underway to evaluate the safety and efficacy of PVP in patients with ongoing OAC therapy. The study results could influence the perioperative management of OACs in BPO surgery with a high level of evidence.

**Trial registration:**

ClinicalTrials.gov, NCT03297281. Registered on 29 September 2017.

## Background

Urologists and anaesthesiologists are routinely challenged by the surgical management of men with benign prostatic obstruction (BPO) who are taking oral anticoagulants (OACs) [1]. The number of patients admitted for surgery who are treated with vitamin K antagonists (VKAs) and direct oral anticoagulants (DOACs) continues to rise. To improve the safety of ageing and frail patients treated with OACs, new “minimally invasive” surgical techniques have recently emerged [2].

Photoselective vaporization of the prostate (PVP) with the GreenLight 532-nm laser (Boston Scientific Corporation, Marlborough, MA, USA) is one of the fastest growing alternatives to transurethral resection of the prostate (TURP) for prostates < 80 ml in the last decade [3]. Initially, GreenLight PVP was introduced as an 80-W system, and increasingly high-powered lasers have since been developed. Several meta-analyses of the 80-W and 120-W high-performance systems (HPSs) report that PVP has similar efficacy and reduced complication rates compared to TURP [4, 5]. In addition, a recent randomized controlled trial (RCT), the “Goliath Study,” reported that PVP using the new 180-W generator Xcelerated Performance System (XPS) provided non-inferior functional outcomes compared to TURP with significantly reduced bleeding complication rates [6–8]. To date, an average of 30% of BPO surgeries are carried out in France using the 180-W XPS laser [9].

In regard to the haemostasis properties of the 532-nm laser [10], several studies have retrospectively investigated the feasibility of PVP without bridging or interrupting OAC treatment, but the amount of evidence remains low and relies on poorly designed studies [11, 12]. Moreover, the consequences of OAC perioperative management on PVP surgical morbidity have never been evaluated in a randomized study. Our objective was to assess the impact of maintaining OAC treatment on perioperative morbidity in patients undergoing PVP.

## Methods/design

### Study design

Stopping or maintaining oral anticoagulation in patients undergoing PVP (SOAP) is a randomized, open-label, multicentre, non-inferiority trial with two parallel groups. Patients will be allocated 1:1 to either the intervention group (S1) or the control group (S2). This study will be conducted in 11 centres in France. This study seeks to assess whether maintenance of OAC treatment increases the risk of adverse events (AEs) in patients undergoing PVP. Postoperative complications will be identified according to the Clavien-Dindo classification [13, 14]. This trial is registered with ClinicalTrials.gov (NCT03297281).

### Inclusion criteria

The criteria for inclusion are as follows: patients with a prostate volume ≤ 80 ml (documented via ultrasonography); patients with bothersome lower urinary tract symptoms (documented with an International Prostate Symptoms Score [IPSS] and uroflowmetry) that are refractory to medical treatment and/or those who have complications related to BPO; patients who are candidates for PVP; patients treated with a VKA for 3 months or longer and with an international normalized ratio (INR) therapeutic range from 2 to 3 or treated with a DOAC for 3 months or longer; patients who are able to comply with all study requirements and have signed a study-specific informed consent form.

### Exclusion criteria

The exclusion criteria for this study are history of prostate cancer, previous pelvic radiotherapy, or stenosis of the urethra; bladder tumour; treatment with antiplatelet agents (other than aspirin); allergy to heparin or history of heparin-induced thrombocytopenia; treatment with an injectable anticoagulant treatment at baseline (e.g. heparin, low-molecular-weight-heparin [LMWH], fondaparinux); mechanical prosthetic heart valve; stroke (ischaemic or haemorrhagic), systemic embolism or transient ischaemic attack (TIA) within past 12 weeks; venous thromboembolism (deep vein thrombosis and/or pulmonary embolism) within past 12 weeks; major bleeding within past 6 weeks; severe renal insufficiency (calculated creatinine clearance < 30 ml/min); thrombocytopenia (platelet count < 100 × 10^9^/L); life expectancy < 1 month; a condition that impairs compliance with the trial protocol (e.g. cognitive impairment, an uncontrolled psychiatric condition, geographic inaccessibility); contraindication to PVP surgery; or contraindication to general anaesthesia.

### Randomization

The surgeon will perform patient randomization at the time of the inclusion visit. The numbers of the two strategy groups will be balanced with a ratio of 1:1. Randomization will be stratified by the investigation centre and by the indwelling catheter at the time of surgery, which is known to be an independent factor of perioperative morbidity [15]. The randomization will be performed by a central randomization system, and allocation of the strategy will be performed by a minimization method to ensure well-balanced groups [16].

### Study intervention

#### Surgical procedure

The elective surgical procedure will be performed after approval of the surgeon and anaesthesiologist, and the surgery will be performed according to the usual indications of the PVP technique. The surgical procedure will be performed under general anaesthesia, owing to the OAC treatment. PVP will be carried out according to the technique described by Malek et al. [17] using a GreenLight XPS 180-W device (Boston Scientific Corporation) and a MoXy fibre inserted through the working channel of a continuous double-flow 23-Ch or 26-Ch cystoscope with 0.9% saline irrigation. Urine sterility will be analysed before the surgery. Asymptomatic bacteriuria (with or without an indwelling catheter) will be treated with an appropriate antibiotic for at least 48 h before the surgery. If a case of urethral meatus stenosis makes the introduction of the cystoscope difficult, atraumatic dilatation will be preferred rather than performing an urethrotomy to avoid bleeding in the patients under ongoing OAC treatment.

#### Management of anticoagulation treatment during the perioperative course

This study focuses on perioperative OAC management for BPO surgery with PVP (Fig. 1). Only OAC therapies, including VKAs and DOACs, are considered in this trial. Patients taking antiplatelet agents (other than aspirin) will be excluded.

**Fig. 1 Fig1:**
[figure not shown]
Flow diagram of the study design. Patients will be randomly allocated in a 1:1 ratio to the OAC group (S1) or the control group (S2)

Both strategies are presented in Fig. 2. The interventional group (S1) includes patients taking an OAC until the day of the surgery. OAC treatment will be resumed the day after surgery. The control group (S2) includes patients who will stop OAC treatment before surgery according to the French anaesthesiology guidelines, which state that if a patient is taking a VKA or dabigatran, treatment will be stopped 5 days before the procedure. If the patient is treated with a DOAC other than dabigatran, treatment will be stopped 3 days before PVP surgery. The postoperative prescription of a prophylactic or a curative dose of LMWH is left to the discretion of the anaesthesiologist. OAC treatment will be resumed when haemostasis is achieved, which will be judged as appropriate and safe enough by the surgeon. However, we recommend resuming OAC treatment as early as possible in the postoperative course.

**Fig. 2 Fig2:**
[figure not shown]
Study protocol

### Data collection and follow-up

The patients’ baseline demographics and medical history will be collected. All patient data will be collected on an electronic case report form (eCRF). The following data will be collected as scheduled (see Table 1): consent, complete biological assessments, urinary culture analysis, prostate-specific antigen (PSA) level, prostatic ultrasound measurement, uroflowmetry (Qmax), IPSS, Urinary Symptom Profile (USP) score, CHA_2_DS_2_-VASc score, HAS-BLED score, ATRIA bleeding risk score, treatments including OAC treatment, intraoperative data and immediate postoperative AEs.

**Table 1 Tab1:** Standard protocol items

	V1 Baseline M-1	Hospitalization			V2 1 month follow-up +/− 7 days	V3 3 months follow-up +/− 7 days	V4 6 months follow-up +/− 7 days
		D-1	Discharge	D0			
Patient information	✓						
Informed consent	✓						
Verification of eligibility criteria	✓						
Randomization	✓						
Clinical examination	✓					✓	✓
Complete biological check-up		✓			✓		
CBEU	✓				✓	✓	✓
PSA	✓					✓	✓
Ultrasound: measurement of prostatic volume and post-voiding residual	✓					✓	
Uroflowmetry: measurement of Qmax	✓					✓	✓
IPSS and USP questionnaires	✓				✓	✓	✓
Collection of patient data	✓						
Collection of operative data				✓			
Scores: CHA_2_DS_2_-VASc, HAS-BLED, ATRIA bleeding risk		✓			✓		
Collection of treatments	✓			✓	✓	✓	✓
Collection of adverse events			✓	✓	✓	✓	✓

Patients will be followed up to 6 months after PVP surgery, with three visits scheduled at 1 month, 3 months and 6 months after the surgery. The urologists will perform the follow-up and will be responsible for collecting all of the data needed for the study, including data on any AEs that will be classified according to the Clavien-Dindo classification.

Monitoring visits will be scheduled in the centres to verify patient consent, protocol compliance and data quality. These visits will be adapted to the rhythm of the included centres.

### Outcome measures

The primary outcome is the number of patients with at least one complication classified greater than or equal to grade 2 according to the Clavien-Dindo classification at the 30 days follow-up. An independent adjudication committee composed of two surgical urologists will meet every 6 months to review the AEs and to validate the judgement criteria. This committee will be blinded to the randomization.

Secondary outcomes are the number of patients with at least one complication classified as greater than or equal to grade 2 according to the Clavien-Dindo classification at 6 months and the number of patients with at least one haemorrhagic or thrombotic complication at 1 month and 6 months. Moreover, the duration of catheterization, the length of hospital stay, the prostatic residual volume, PSA level, IPSS score, IPSS question 8 and USP, uroflowmetry (Qmax) and post-voiding residual will be collect during the follow-up visits.

Bleeding complications are defined as follows: a significant and persistent haematuria in a patient with or without a urethral catheter (Clavien 2) leading to a decrease in haemoglobin of 2 g/dl or more; a gross haematuria requiring clot removal through the bladder catheter under local anaesthesia (Clavien 3a) or with a cystoscope under general anaesthesia (Clavien 3b); and bleeding appearing in the immediate postoperative course, with the requirement of a red blood cell transfusion (Clavien 2).

As the Clavien-Dindo classification is not accurate enough to report postoperative thrombotic events, we choose the same definition of thrombotic complications described in the BRIDGE study [18]. The first is a stroke, where either of the following criteria must be satisfied: any new, focal neurologic deficit that persists for > 24 h or any new, focal neurologic deficit of any duration and with evidence of acute infarction on computed tomography (CT) or magnetic resonance imaging (MRI) of the brain. The second is a TIA, where the following criteria must be satisfied: any brief neurologic deficit caused by focal brain or retinal ischaemia, with clinical symptoms lasting, typically, for < 1 h and not for > 24 h; no evidence of acute infarction on CT or MRI of the brain; and no signs of acute myocardial infarction on CT scan or MRI. The third thrombotic complication is a systemic embolism, where all three of the following criteria must be satisfied: a symptomatic embolic episode associated with an abrupt arterial insufficiency to the upper extremity, lower extremity or abdominal visceral organ; the embolism is verified by intraoperative or radiologic evidence (e.g. CT angiography) of an arterial occlusion; and the embolism occurs in the absence of other likely mechanisms (e.g. atherosclerosis).

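### Transfused bleeds count only if they appear in the immediate postoperative period, although haemorrhagic complications are counted to 1 and 6 months; isolated haematuria also depends on an unscheduled haemoglobin

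*Protocol article*

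**What the plan says.** Outcome measures in the protocol article defines bleeding complications by three routes:

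- Significant, persistent haematuria (labelled Clavien 2) "leading to a decrease in haemoglobin of 2 g/dl or more". No time limit.
- Clot removal: "a gross haematuria requiring clot removal through the bladder catheter under local anaesthesia (Clavien 3a"), or by cystoscope under general anaesthesia (3b). No time limit and no laboratory value.
- Transfusion: "bleeding appearing in the immediate postoperative course, with the requirement of a red blood cell transfusion (Clavien 2"). This is the only route with a time limit, and the period is not defined in days.

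The same section makes the primary outcome any Clavien-Dindo complication of grade 2 or higher by 30 days. A secondary outcome counts patients with a haemorrhagic or thrombotic complication at 1 month and at 6 months.

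In Table 1 (Data collection and follow-up) the row "Complete biological check-up" is ticked at D-1 and at V2 (1 month ± 7 days) only. Adverse events are collected at D0, discharge and every follow-up visit.

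Study design describes a "randomized, open-label, multicentre, non-inferiority trial with two parallel groups". On data collection: "The urologists will perform the follow-up and will be responsible for collecting all of the data needed for the study". On the adjudication committee: "This committee will be blinded to the randomization".

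**The concern.** The transfusion criterion and the outcome it feeds cover different periods. A bleed in, say, the third week that leads to red-cell transfusion is a serious event in a trial about continuing anticoagulation. As written, it is a bleeding complication only if it also satisfies one of the two untimed routes. Under the section on management of anticoagulation, S1 resumes OAC the day after surgery, while S2 resumes when the surgeon judges haemostasis adequate. The period at risk of bleeding on resumed treatment therefore starts at different times in the two arms, and a cut-off tied to the early postoperative period can remove different shares of events from each.

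The second concern is narrower. For haematuria with neither clot removal nor transfusion, the haemoglobin criterion needs a measured value. None is scheduled between D-1 and about 1 month, so a fall that has recovered by V2 is seen only if someone who knows the allocation orders a count. The blinded committee can judge a reported fall but cannot recover one that was never measured.

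**Working it through.** **1. Which late bleeds are lost (bleed after the immediate postoperative period, within 1 or 6 months)**

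| Late event | Route | Bleeding complication as written? |
|---|---|---|
| Clot removal by catheter or cystoscope | 3a / 3b | Yes |
| Persistent haematuria, measured fall ≥ 2 g/dl, transfused or not | Haematuria | Yes |
| Transfused bleed, neither of the above | Transfusion, but time-limited | No |
| Persistent haematuria, no count taken, no transfusion or clot removal | Haematuria, criterion not documented | No |

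The third row is the main gap and the fourth is the secondary point.

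**2. Size of the main gap.** The documents give no rate for the third row. With 386 patients randomised 1:1 there are 193 per arm. If 1% have such a bleed and no other counted event (assumed), 0.01 × 193 = 1.93, about 2 per arm. At 3% (assumed), 0.03 × 193 = 5.79, about 6 per arm.

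**3. The plan's own sample size.** Inputs from Sample size estimation: 13.2% in both arms, margin 10 points, two-sided 95% interval, 80% power.

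n per arm = (1.96 + 0.8416)² × 2 × 0.132 × 0.868 / 0.10² = 180, so 360 in total, against the stated figure of approximately 350. Power at 175 per arm is 78.9%. The plan's figure is reproduced closely enough to use 175 per arm below.

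**4. Sensitivity of the primary comparison to haemoglobin testing (assumed inputs).** Let h be the share of primary events visible only through a haemoglobin test, and d1 and d2 the shares of those detected in S1 and S2. The observed risk is the true risk × [1 − h(1 − d)]. The chance of concluding non-inferiority is Φ[(0.10 − (p1 − p2))/SE − 1.96], with SE = √[p1(1 − p1)/175 + p2(1 − p2)/175].

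With true risks at the margin (S1 23.2%, S2 13.2%) and full detection, this is 2.5%. Example with h = 0.25 and d = 0.5 in both arms: p1 = 0.232 × 0.875 = 0.203, p2 = 0.132 × 0.875 = 0.1155, difference 0.0875, SE 0.0388, result 5.1%.

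| h (assumed) | d1 = d2 = 0.5 | d1 = 0.5, d2 = 0.75 | d1 = 0.75, d2 = 0.5 | Power, d1 = 0.75, d2 = 0.5, true risks equal |
|---|---|---|---|---|
| 0.10 | 3.3% | 4.0% | 2.4% | 77.5% |
| 0.25 | 5.1% | 7.6% | 2.2% | 75.3% |
| 0.50 | 10.1% | 19.7% | 1.9% | 71.4% |

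Columns 2 to 4 give the chance of a false non-inferiority conclusion; the last column compares with 78.9%.

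A simpler illustration: if 5% of patients have a true fall that only a test would reveal, detected in 90% of one arm and 60% of the other, the difference shifts by 0.05 × (0.90 − 0.60) = 0.015, that is 1.5 points or 15% of the margin. All three inputs are assumed.

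**The case against.** Several counter-arguments have force.

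- **Late transfused haematuria usually counts anyway.** The haematuria route has no time limit, and a patient bleeding enough to be transfused will normally have a blood count. This stands, and it reduces the gap to bleeds that fit neither untimed route.
- **The primary endpoint is broader than the bleeding definition.** A reader might infer that late transfused bleeds drop out of the primary analysis. The documents do not support that: the primary endpoint is any grade 2 or higher complication, the plan itself grades a transfused bleed as 2, and nothing removes a later one. Nor does it say expressly that a later one enters.
- **Most bleeding does not hinge on a test.** A reader might infer that bleeding detection as a whole depends on who orders a count. It does not: grade 3a/3b and transfused events need no haemoglobin value. Even for isolated haematuria a visible sign comes first, so testing is event-driven in the ordinary way.
- **The grade label is ambiguous.** It stands before the haemoglobin clause, so the fall may be needed only for the bleeding label and not for grade 2. If so, the effect on the primary endpoint is smaller still.
- **The article condenses a full protocol.** Further in-hospital sampling may be specified there. This weakens the secondary point, although the printed schedule shows none. It does not touch the transfusion wording, which is an explicit rule.
- **The illustration is unanchored.** Five per cent of patients would be 5/13.2 = 38% of all expected primary events, and no passage supports that share.

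**Conclusion.** The main point holds for the haemorrhagic secondary outcome: its transfusion criterion is limited to early bleeding while its windows run to 1 and 6 months. Read literally, a late transfused bleed is omitted when there is neither clot removal nor haematuria with a documented fall of 2 g/dl or more. The number is probably small and cannot be estimated from the documents. It could differ by arm because OAC resumption is timed differently. For the primary endpoint the wording leaves doubt but is not a demonstrated loss.

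The secondary point holds only for isolated haematuria without clot removal or transfusion. Detection of the fall between D-1 and 1 month rests on an unscheduled count in an open-label trial. More testing in S1 would work against non-inferiority and less testing in S1 would favour it. Equal under-detection shrinks a true difference. The documents fix neither direction nor size, so the sensitivity table and the 1.5-point shift show how the mechanism works and are not estimates of bias in this trial.

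**What to change.** 1. Delete the time limit from the transfusion criterion, so that any bleed requiring red-cell transfusion within the 1-month and 6-month windows is a bleeding complication in both arms. State in the same place that it counts as grade 2 for the primary endpoint up to day 30. No new visit is needed, since adverse events are already collected at every follow-up visit. The small downside is a change of outcome wording after recruitment began (30 of 386 enrolled at 30 September 2018). It should be dated, made without sight of results by arm, and applied by the blinded committee to patients already enrolled.

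2. As a secondary improvement, add to Table 1 one haemoglobin at a fixed in-hospital time point, for example discharge, for every patient, compared with D-1. This would equalise in-hospital detection at the cost of one blood count per patient during an existing stay. It would not detect bleeding after discharge. For that, recording the date and reason of each unscheduled haemoglobin would at least allow testing frequency to be compared between arms.

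### The secondary haemorrhagic/thrombotic outcome omits late or untransfused non-urinary bleeds and lets a haemorrhagic stroke count as thrombotic

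*Protocol article*

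**What the plan says.** All of the definitions are in the protocol article, under Outcome measures.

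- **Outcome and window.** The secondary outcome is "the number of patients with at least one haemorrhagic or thrombotic complication at 1 month and 6 months". The Methods paragraph of the abstract words it differently: "The secondary endpoint will examine the 30-day rate of haemorrhagic and thrombotic events".
- **Bleeding.** Three criteria are listed. The haematuria criterion asks for persistent haematuria with a haemoglobin fall of at least 2 g/dl. The clot criterion is "a gross haematuria requiring clot removal through the bladder catheter under local anaesthesia (Clavien 3a"), and cystoscopic removal is graded 3b. The transfusion criterion is "bleeding appearing in the immediate postoperative course, with the requirement of a red blood cell transfusion (Clavien 2").
- **Stroke.** It is listed as a thrombotic complication, using a definition taken from the BRIDGE study. Either of two criteria suffices. One is "any new, focal neurologic deficit that persists for > 24 h"; the other is a deficit of any duration with infarction on brain imaging.
- **Exclusion criteria.** Here the article names both stroke types: "stroke (ischaemic or haemorrhagic), systemic embolism or transient ischaemic attack (TIA) within past 12 weeks".

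**The concern.** The trial compares maintaining with interrupting oral anticoagulation. That choice can shift bleeding and thrombosis in opposite directions, and the bleeding need not come from the prostate. The article's Discussion itself describes the hazards of anticoagulation and of its interruption without restricting them to the urinary tract.

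The haemorrhagic/thrombotic outcome is the one place where the trade-off can be read by cause, because the Clavien-Dindo outcomes do not separate bleeding from thrombosis. If its rules leave out some bleeds and place others under thrombosis, the balance between the two harms is misreported. The bleeding list also does not match its own window: the only criterion open to a non-urinary site ends with the immediate postoperative course, while the outcome runs to 6 months.

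**Working it through.** No figure in the plan bears on this point, so the check applies the written rules to example events. The inputs are the three bleeding criteria, the two stroke criteria, and the any-cause outcomes (at least one complication of Clavien-Dindo grade 2 or higher, at 30 days and at 6 months).

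| Event | Bleeding list | Thrombotic list | Any-cause grade ≥ 2 outcomes |
|---|---|---|---|
| Intracranial haemorrhage with focal deficit > 24 h, after the immediate postoperative course | No | Yes, as stroke | Yes, if graded ≥ 2 |
| Intracranial haemorrhage without a focal deficit > 24 h, not transfused in the immediate postoperative course | No | No | Yes, if graded ≥ 2 |
| Gastrointestinal or other non-urinary bleed on day 10, transfused | No | No | Yes (the article labels transfusion Clavien 2) |
| Non-urinary bleed at any time, not transfused, no focal deficit | No | No | Yes, if graded ≥ 2 |
| Non-urinary bleed in the immediate postoperative course, transfused | Yes | No | Yes |

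**Bleeding.** The first two criteria require haematuria, so they cannot admit another site. The third is limited by both time and transfusion. Rows 2 to 4 fall outside all three.

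**Stroke.** The neighbouring definitions each contain a cause: the second stroke criterion needs infarction, TIA needs focal brain or retinal ischaemia, and systemic embolism needs a verified arterial occlusion. Only the 24-hour criterion has none. Because either stroke criterion suffices, row 1 is a thrombotic stroke on the text. It is also a bleed only in the unusual case of transfusion in the immediate postoperative course.

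**Effect under each reading of the outcome.** If haemorrhagic and thrombotic complications form one composite, row 1 is still counted once and nothing is on the wrong side; only rows 2 to 4 matter. If the components are reported separately, row 1 is also wrong: one event is taken from bleeding and added to thrombosis. The abstract's wording and the two separate sets of definitions suggest separate reporting but do not settle it.

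**The case against.** **The events are not lost from the trial.** This stands. Adverse events are collected up to the 6-month visit, a committee blinded to allocation reviews them, and both any-cause outcomes count them when graded 2 or higher. A reader might infer that the primary comparison under-counts bleeding; the documents do not support that.

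**Surgical-site bleeding is a defensible target.** The rationale is the laser's local haemostatic effect. This stands in part: the urological criteria are worth keeping. But the outcome is labelled haemorrhagic complications without a site, and its third criterion names no site, so the text does not present a deliberate surgical-site outcome.

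**The committee could refuse to call a haemorrhagic stroke thrombotic, and the cited source may require an ischaemic cause.** Both are possible, and the source cannot be checked here. It would be too strong to say that such events will be miscounted. What can be said is that the written rule admits them and gives no ground for moving them. The exclusion criterion is only modest support: it shows that the distinction was known, but it puts both stroke types under one rule.

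**The size is conjecture.** This stands. A reader might assume a thrombotic rate of 0.5–1% and compute 193 × 0.005 = 1.0 to 193 × 0.01 = 1.9 events per arm (386 / 2 = 193), so that one misplaced event would shift an arm's count by about 50–100%. The rate is not in the documents and the event is supposed, so the figure says nothing about how likely the problem is.

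**The TIA wording.** The requirement of "no signs of acute myocardial infarction on CT scan or MRI" looks out of place for a brain or retinal event. It is a wording slip with no shown effect on the classification of bleeding or stroke, and the point does not rest on it.

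**Conclusion.** The point holds for the cause-specific secondary outcome. As written, its bleeding list omits non-urinary bleeds that occur after the immediate postoperative course or are not transfused. Its 24-hour stroke criterion lets a haemorrhagic stroke count as thrombotic, normally without counting as bleeding. The omission applies under either reading of the outcome; the wrong-side count matters only when the two components are reported separately.

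The primary outcome, the 6-month Clavien-Dindo outcome and the sample size are unaffected. The documents give no rate for non-urinary or intracranial bleeding, so the size cannot be computed. The net direction between arms is also unknown, because heparin use in the control arm may affect bleeding too. The conclusion assumes that the listed criteria are exhaustive, as their wording as a definition implies, and that the committee applies them as written. The change should be made because these are rules stated in the article and they are cheap to correct.

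**What to change.** Amend the outcome definitions, and the adjudication rules to match:

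1. Define a haemorrhagic complication as any adjudicated bleeding event of Clavien-Dindo grade 2 or higher, at any site and any time within the 1-month or 6-month window. Keep the present urological criteria as a named subset, so that the narrower result can still be reported.
2. Require an ischaemic cause for thrombotic stroke and count intracranial haemorrhage as haemorrhagic. State how a stroke of undetermined type will be listed, since the reviewing committee consists of two urologists.
3. State that the haemorrhagic and thrombotic components are reported separately, whether or not a composite is also given.
4. Tidy the TIA wording in the same amendment.

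No new data collection is foreseen, because adverse events are already recorded to 6 months, graded and reviewed blind. The cost is a formal change of outcome definition during recruitment of an open-label trial. At the date given under Trial status and timeline, 30 of 386 patients (30 / 386 = 7.8%) were enrolled, so re-adjudication would be limited to the few early cases.
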